## Abstract

**Background:**

Informal care is a social challenge that impacts the daily life and quality of life (QoL) of caregivers. While care has evidence of positive aspects, it can also have negative impacts on mental, physical, economic, and social well-being. Nowadays, health, social, and care systems for informal caregivers are needed, from a person-centered perspective, to promote their QoL, health, and empowerment. Technology is a promising tool to provide personalized services.

**Objective:**

This study aims to develop an innovative care-centered technology solution to enhance caregivers’ QoL, care impact, occupational balance, health self-management, and empowerment.

**Methods:**

A mixed methods pilot trial was designed as a single-arm open-label study. Participants will be caregivers of people with disabilities or older people, recruited through direct care centers. Caregivers will engage in a participatory process of developing, testing, and validating the TechQoL4Carers project platform, *CuidaconTIC*; a web-based platform to improve their QoL, impact of care, occupational balance, health self-management, and empowerment. The development of this trial will refine the *CuidaconTIC* platform, which is based on person-centered development, participatory design techniques, and an iterative process. A total of 54 caregivers will participate in a 3-month intervention involving the use of the *CuidaconTIC* platform and the Xiaomi Smart Band 7 wristband. Standardized assessment tools (EQ-5D-5L, Care-Related Quality of Life, Zarit Burden Interview, Caregiver Strain Index, Occupational Balance Questionnaire-Spanish Version, Psychological Empowerment Instrument, and the System Usability Scale) and a self-designed tool (Satisfaction-Q) will be used at 3 time points to collect information about usability, satisfaction, and project variables. Continuous information will be obtained from the platform (My week-Q) and the wearable wristband (physical activity and sleep). An interview will be conducted to gain in-depth knowledge about participants’ perspectives. This study was approved by the Ethics Committee for Research and Teaching of the Universidade da Coruña (2023_019) and registered on ClinicalTrials.gov. Participation will be entirely voluntary, with informed consent obtained from each participant. Detailed information sheets and informed consent forms will be provided. The data of the participants will be collected in a pseudonymized form. Once the study has been completed, any possibility of participant identification will be eliminated.

**Results:**

Financial support for this project was received on December 1, 2022. This protocol was submitted after data collection but before analysis. Data collection began in May 2024 and ended in March 2025. By October 2025, 62 participants had been recruited. We expect to publish our results in June 2026.

**Conclusions:**

This protocol focuses on the study of the social challenge of quality of life of caregivers, mostly women, and on reducing the digital gap and promoting inclusion, through a service that places people and care at the center.

## Introduction

### Background and Rationale

Care is considered an occupation in daily life, encompassing a wide range of responsibilities linked to support in activities of daily living and/or instrumental activities of daily living [1,2]. In this regard, informal care, often provided by family members, plays a crucial role in providing support to individuals with long-lasting needs (chronic illnesses, disability, age-related dependency, among others), and in many cases, they must face decision-making together with health and social services [3,4].

In recent years, the combination of social, demographic, and economic factors has increased informal care across Europe [5]. Statistics indicate that approximately 14.4% of the European population aged 18 to 74 are informal caregivers, providing up to 80% of all long-term care for dependent individuals [6]. In particular, Spain is among the European countries with the highest prevalence of informal caregivers, with 15.3% of the population engaged in this role and 52.9% of informal caregivers dedicating more than 20 hours per week to care [7,8]. Furthermore, literature states that the most common profile of an informal caregiver is a woman (n=32,590, 63.28%) aged between 45 and 64 years (n=18,814, 55%) [6,9].

Although care can be a source of great personal satisfaction, it also poses numerous challenges [10]. Caregiving tasks can significantly impact the quality of life (QoL), well-being, and health of informal caregivers. The burden of long-term care may lead to physical and cognitive difficulties, as well as mental health issues [10,11].

Evidence suggests that women, older caregivers, and spouses are likely to experience high levels of stress related to their care roles [9,12]. Factors such as task overload, insufficient support, financial difficulties, restrictions in daily activities, and social exclusion can lead to chronic stress [13,14]. This prolonged situation, when combined with high levels of emotional exhaustion, sleep disturbances, and physical issues, can lead to “caregiver’s burnout syndrome or caregivers’ burden” phenomenon [13,15]. Additionally, mental health issues are approximately 20% more prevalent among informal caregivers than noncaregivers, especially among those who provide intensive care (more than 20 h/wk) [5,16].

Informal care is also related to occupational balance, habits, and routines of the caregiver. Providing informal care directly affects the caregiver’s daily life [17]. Some authors mention that care responsibilities can be a barrier to accessing education and paid employment [17,18]. In fact, many caregivers, due to difficulties in reconciling work and care duties, may be forced to reduce their working hours and/or leave paid employment, leading to financial, social, and personal difficulties [10,19]. Specifically, statistical data suggest that women aged between 35 and 44 are most affected by this situation, finding themselves obliged to reconcile with part-time employment (60.2%) or to stop working (31.4%) [8].

Furthermore, caregivers also face challenges in dedicating time to other meaningful occupations and maintaining their healthy lifestyle habits [2,17]. Specifically, statistical data shows that Spanish caregivers have reduced their leisure activities by 77%, their time for social participation by 47.88%, and their time for personal self-care by 60.34% [8].

In this way, the repercussions of care can make informal caregivers susceptible to health issues that may lead to chronic diseases [11]. Furthermore, the increase in the number of older informal caregivers also highlights the need for social and health care support for them [5]. These circumstances, along with the implementation of person-centered care (PCC) principles, underscore the importance of decision-makers, policymakers, and professionals recognizing, respecting, and supporting informal caregivers by seeking and developing cost-effective, sustainable, and preventive solutions [20,21].

Various studies have focused on the development of intervention programs aimed at reducing care burden, providing social support, or improving caring skills [1,14,19]. However, despite their potential, these programs have some limitations related to difficult access, lack of information, or insufficient support for caregivers to participate effectively [16]. Consequently, there is a need for innovative methods that eliminate these barriers [22]. Thus, Information and Communication Technologies offer the possibility to provide support and services to caregivers in real time [22].

In recent years, the development and evaluation of technological solutions aimed at the informal caregiving population has become an area of growing interest [23]. The literature highlights that tools such as mobile applications, online educational programs on caregiving, health monitoring devices, task management systems, and emotional support networks are accepted by informal caregivers as they facilitate the management of care, improve the quality of care, reduce emotional and physical burden, and enhance their well-being [20,24].

In this regard, Tan et al [25], in their scoping review, report that the use of technological tools by informal caregivers contributes to a reduction in caregiving burden and a slight improvement in the quality of life of caregivers. While various studies emphasize the benefits of digital solutions to improve adherence to treatments for dependent individuals, optimize care task management, and highlight the importance of home assistive technology [26].

Despite advancements in the implementation of technological solutions, significant barriers to their adoption remain, particularly among older caregivers [25]. Studies such as those conducted by Egan et al [27] and Xiong et al [28] point out certain concerns of informal caregivers. These include fears that these technologies may replace human contact, a lack of familiarity with these technologies, the costs associated with some applications or technological services, the lack of technological adaptation, sustainability, the rapid evolution of technology, as well as the design and usability of these systems.

Furthermore, many mobile applications do not offer personalized content, leading caregivers to perceive the information as irrelevant or overly complex for their needs [29]. As noted by Premanandan et al [30], current technological solutions primarily focus on managing the care of dependent individuals but fail to address the specific needs of the caregivers themselves. This trend is particularly evident in studies centered on caregivers of individuals with dementia, where Information and Communication Technologies solutions have been designed without a comprehensive approach that also considers the emotional and well-being needs of informal caregivers [31]. Additionally, some applications aimed primarily at caregivers, such as the CareFit app, which encourages caregivers to engage in regular physical activity at home, have limitations, including the lack of time caregivers have to carry out activities, difficulties in understanding how to perform the activities, and the feeling of insecurity when carrying out those activities at home [32].

Thus, the literature emphasizes the importance of involving informal caregivers in the design and development process of technological solutions to ensure that these meet their needs effectively, are accessible, easy to use, and sustainable in the long term [22,28]. Person-centered design is crucial for improving the health, maintaining the quality of life, and strengthening the well-being of caregivers, which in turn positively impacts the care provided, at health, social, and economic levels [33].

In this regard, this project aims to address these challenges by creating a technological solution that improves the quality of life and health status of informal caregivers, as well as being aware of the implications and repercussions that continuous care has on informal caregivers.

### Aims, Objectives, and Hypotheses

According to the existing literature and the main conclusions of the background, there is a clear need to develop a technological solution specifically designed for informal caregivers. The hypothesis is that this innovative technological solution will have a positive impact on their QoL, impact of care, occupational balance, self-management of health, and empowerment.

The primary objective of this pilot trial is to develop and evaluate an innovative technological solution aimed at enhancing the QoL, impact of care, occupational balance, self-management of health, and empowerment of informal caregivers of older people and/or people with disabilities. The main question is: Will the routine use of the TechQoL4Carers platform have a positive impact on the daily life of informal caregivers?

The specific objectives of this project are (1) to develop an innovative technological solution for informal caregivers aimed to improve their QoL, impact of care, occupational balance, self-management of health, and empowerment; (2) to assess the impact of the platform on the QoL, care, self-management of health, and empowerment of informal caregivers; (3) to test and evaluate the contents, usability, quality, and satisfaction with the platform by informal caregivers; and (4) to identify potential barriers and necessary changes as well as facilitators to use the platform.

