## Methods

### Study Design

A mixed methods pilot trial was designed as a single-arm open-label study. Informal caregivers will participate in a participatory process of developing, testing, and validating a technological platform to improve their QoL, impact of care, occupational balance, self-management of health, and empowerment.

The 3-month intervention will be based on the use of the TechQoL4Carers technology platform, called *CuidaconTIC* [34], and the Xiaomi Smart Band 7 wearable wristband. Formal assessments using standardized tools will be conducted as follows: baseline (preintervention: t_0_), mid-intervention (at 6 wk: t_2_), and postintervention (t_4_).

Throughout the intervention (t_1_ to t_3_), continuous information will be obtained through data from the platform and the Xiaomi wearable wristband. A qualitative evaluation will be conducted to gain in-depth knowledge about participants’ perspectives on the intervention and study procedures (t_4_).

The trial has been registered on ClinicalTrials.gov with the identification number NCT06226285 [35]. As this is research with people, in this case, caregivers, a favorable report has been previously obtained from the Ethics Committee for Research and Teaching of the Universidade da Coruña (code: 2023_019).

In addition, the SPIRIT (Standard Protocol Items: Recommendations for Interventional Trials) statement [36] and the CONSORT-EHEALTH (Consolidated Standards of Reporting Trials of Electronic and Mobile Health Applications and Online Telehealth) guidelines [37] were adopted for the protocol design. A summary of the trial, based on the World Health Organization (WHO) Trial Registration Data Set [38], can be found in Multimedia Appendix 1.

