### Sample Size

To determine the necessary sample size for this study, the G*Power software was used. Based on similar studies and assuming that caregivers’ QoL is the primary outcome of this study (with all other variables treated as secondary and/or exploratory outcomes), power analysis was performed [39]. An a priori power analysis was conducted using a paired t test on the primary outcome, as an improvement in informal caregivers’ QoL was expected after the intervention. A moderate effect size (Cohen *d*=0.5), a significance level of .05, and a statistical power of 80% (1−*β*=.80) were assumed. Under these assumptions, a sample of 54 caregivers who complete the study (*df*=53) provides power greater than 80% to detect the expected effect.

Given the multiplicity of the planned analyses, confirmatory inference will be restricted to the primary outcome. Secondary and exploratory outcomes will be interpreted with caution, without applying a formal adjustment for multiple comparisons, and emphasis will be placed on effect sizes and their 95% CIs.

In addition, an attrition rate of up to 20% is anticipated (due to dropouts, absence from the postintervention assessment, or technical problems with the wearable device or platform). Therefore, we plan to recruit approximately 65 informal caregivers, so that at least 54 are expected to complete the study and be included in the primary analysis.

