### Analysis

The statistical analysis of the data will be performed using R software (version 4.4.3 [63]). All data will be cleaned and processed prior to analysis, and a range of statistical procedures will be performed based on the study hypotheses and objectives. The significance level for hypothesis testing is set at 5%. Numerical variables will be presented as mean and SD, along with range, minimum, and maximum values, while categorical variables will be presented as absolute frequency and valid percentage.

After performing a descriptive analysis of the variables, we will determine the distribution of the data using formal tests of normality: the Kolmogorov-Smirnov or Shapiro-Wilk tests, as appropriate. This will help decide whether parametric or nonparametric statistical methods are used. Parametric tests, such as the paired *t* test, ANOVA, and Pearson correlation, will be used to analyze data if normality is confirmed. Otherwise, nonparametric tests, including the Wilcoxon signed-rank test, Friedman and Spearman rank correlation, will be employed. Pre- and postintervention changes in the primary outcome and in the other continuous variables will be analyzed using a paired Student *t* test or, where appropriate, the Wilcoxon signed-rank test. The effect size of within-subject changes will be estimated using Cohen *d*, in order to quantify the magnitude of the observed changes. In addition, 95% CIs for these effect sizes will be reported. It is important to note that QoL, considered the primary outcome of the study, will be used for formal confirmatory inference to control the type I error rate; analyses of other outcomes will be considered secondary or exploratory.

In addition, exploratory correlation analyses will be conducted to examine relationships both among the different outcomes from the tools and between these outcomes and summary measures of the biometrical parameters recorded by the wearable devices. Depending on the distribution of the variables, Pearson or Spearman correlation coefficients will be used. For these analyses, the correlation coefficient r and its 95% CI will be reported as the primary measure of effect size. To explore relationships between categorical variables, the chi-square test will be applied. When expected cell frequencies are low, the Fisher exact test will be used instead.

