## Discussion

### Anticipated Findings

This study aims to develop and evaluate an innovative technological solution aimed at enhancing the QoL, impact of care, occupational balance, self-management of health, and empowerment of informal caregivers of older people and/or people with disabilities.

Technology, empowerment, and the PCC framework can help to improve the caregiver’s health status, QoL, and self-management of their own health. These benefits could extend to the care recipients. Hence, caring for the caregiver has a double effect and greater impact on the social and health systems [68]. The PCC approach is a core element of this research, widely studied in health sciences [21,69,70]. The design and development of the *CuidaconTIC* platform will study the eight PCC dimensions: (1) respect for individuals’ values, preferences, and expressed needs; (2) provision of information and education; (3) access to care; (4) emotional support; (5) involvement of family and friends; (6) continuity and safe transitions; (7) physical comfort, and (8) care coordination.

Person-centered technology has significant potential to support informal caregivers. However, most existing technological solutions primarily focus on care recipients, aiming to promote their autonomy, improve their QoL, and consequently, reduce the burden on caregivers [33,71]. Although there are initiatives targeted at caregivers, they tend to be designed for specific groups, such as caregivers of older adults with dementia, or they primarily provide training and informational services without addressing the broader needs of informal care.

Following a comprehensive analysis of health care and social challenges faced by informal caregivers, this study will propose alternative solutions using person-centered technology. This approach will help advance the field of care and technology as a tool to support caregivers in their daily life.

If the initial hypothesis is confirmed, the study will move toward exploring a low-cost intervention with minimal time requirements, oriented in particular for people with limited availability.

To our knowledge, this is one of the first studies that places informal caregivers at the center of technological development, involving them in an iterative process to create a tool that not only improves care but also directly supports their own QoL, the impact of care, occupational balance, self-management of health, and empowerment.

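### The paired before-after test of QoL in a single arm can show change from baseline to t4, but cannot confirm the hypothesis that the platform has a positive impact

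*Protocol article*

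**What the plan says.** Under Aims, Objectives, and Hypotheses, the Protocol article states a causal hypothesis: "The hypothesis is that this innovative technological solution will have a positive impact on their QoL, impact of care, occupational balance", followed by two further domains. The main question is causal too ("The main question is: Will the routine use of the TechQoL4Carers platform have a positive impact on the daily life of informal caregivers"), and so is specific objective 2: "to assess the impact of the platform on the QoL, care, self-management of health, and empowerment of informal caregivers".

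Study Design fixes the comparison: "A mixed methods pilot trial was designed as a single-arm open-label study". Study Design and Intervention both describe the intervention as the platform and the wristband together, given to every participant.

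The test is in Analysis: "Pre- and postintervention changes in the primary outcome and in the other continuous variables will be analyzed using a paired Student *t* test", with the Wilcoxon signed-rank test as the alternative. Sample Size says that "confirmatory inference will be restricted to the primary outcome", and Analysis says that QoL "will be used for formal confirmatory inference to control the type I error rate".

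Anticipated Findings then links the result to a next step: "If the initial hypothesis is confirmed, the study will move toward exploring a low-cost intervention with minimal time requirements".

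**The concern.** The hypothesis and the test address different things. The hypothesis concerns an effect of the platform. The null of a paired test is that mean QoL is the same at baseline and at t4. Rejecting that null shows that QoL changed on average. It does not show why.

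The article as shown has no control group, repeated baseline or external benchmark that would separate the platform from other sources of change, and it carries no caveat on this. Participants know what they receive, the primary instruments are self-administered, and everyone gets the wristband as well as the platform. A general improvement over the study period, more favourable reporting by people who take part in developing and validating the platform, or an effect of the wristband alone would all enter the paired difference.

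What is at stake is the headline conclusion. Read as written, a significant paired test would count as confirmation that the platform works, at an error rate that the test does not guarantee for that statement.

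**Working it through.** **Inputs.** From Sample Size: paired t test, Cohen d = 0.5, significance level .05, 54 completers (df = 53), power stated as above 80%. From Abstract and Results: 62 recruited. Sidedness is not stated, so two-sided 5% is assumed. The calculation is for one test of one QoL score. The size of any non-platform improvement is not in the article and is varied as an assumption.

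**Step 1: reproduce the stated power.** For a paired t test, power comes from the noncentral t distribution with df = n − 1 and noncentrality d × √n. With n = 54 and d = 0.5, the noncentrality is 0.5 × 7.348 = 3.674, and power is 95.0% two-sided (97.6% one-sided). The statement of more than 80% is correct. 80% power would need 34 completers two-sided.

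**Step 2: smallest significant change.** The critical value of t on 53 df is 2.006. The smallest observed standardised change that is significant is 2.006 / √54 = 2.006 / 7.348 = 0.273 SD of the differences.

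**Step 3: probability of a significant improvement with no platform effect.** Set the platform effect to zero and let QoL improve for other reasons by δ, in SDs of the differences. The probability is P(T > critical value), where T is noncentral t with noncentrality δ × √n.

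| Assumed δ | Noncentrality at n = 54 | n = 54 | n = 62 |
|---|---|---|---|
| 0 | 0 | 2.5% | 2.5% |
| 0.1 | 0.735 | 10.8% | 11.8% |
| 0.2 | 1.470 | 30.3% | 34.1% |
| 0.3 | 2.205 | 58.1% | 64.2% |

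The reference value is 2.5%, because only a significant change in the favourable direction would be read as supporting the hypothesis. The column for 62, which is everyone recruited, shows that a larger sample does not help: it makes a non-platform shift easier to detect.

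**Step 4: could the present sample carry a controlled test?** Assume a between-arm difference of 0.5 SD of the analysed score, two-sided 5% and 80% power. An exact two-sample t test then needs 64 per arm, so 128 completers, or 128 / 0.80 = 160 recruited at 20% attrition. 54 completers split 27:27 would have about 44% power. With data collection over, the remedy lies in the conclusion and not in the design.

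**The case against.** The strongest reply is that the word confirmatory is doing a narrower job. Sample Size introduces it because of the number of planned analyses, and Analysis contrasts QoL with secondary and exploratory outcomes. In both places it ranks endpoints for multiplicity. A reader might infer that the article claims type I error control for causal attribution, but neither section says so. Analysis also already speaks of within-subject changes with effect sizes and 95% CIs, and the single arm is declared openly. This stands, and it limits the repair to wording. It does not remove the problem, because the Discussion ties confirmation to the initial hypothesis, and that hypothesis is about the platform's impact.

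Several stronger readings are tempting, and the article does not support them:

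- **Regression to the mean.** Centers preselect candidates, but no entry threshold on QoL or burden is stated, and caregivers with less than one year in the role are excluded. It is possible, not shown.
- **Season.** Data collection ran from May 2024 to March 2025. Staggered enrollment could average a seasonal shift out; the text does not allow a check.
- **The wristband as an undeclared co-intervention.** It is a declared part of the intervention and its data feed the personalized content. It confounds only the narrower wording about the platform, not the effect of the package.
- **A single arm as unsuitable throughout.** It suits the objectives on usability, satisfaction, barriers and facilitators.
- **An established false claim.** That a non-specific improvement would be published as proven benefit is a prediction. The next step in the Discussion is itself exploratory.

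The interviews also bear on daily life, so the paired test is not the only evidence on the main question, though interviews do not replace a comparator. Finally, the assumed shifts are generic and all favourable; a worsening over time would hide a benefit instead.

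**Conclusion.** The point holds as a mismatch between the stated hypothesis and what the only confirmatory test can establish. Type I error is controlled for no mean change in QoL from baseline to t4, and for nothing beyond that. With 54 completers, a change of 0.27 SD of the differences suffices for significance. Non-platform improvements of 0.1 to 0.3 SD would give a significant improvement with probability of about 11% to 58%, against a nominal 2.5%.

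Those probabilities rest on a two-sided 5% test of one score, 54 completers and assumed shifts. They show how sensitive the conclusion is; they are not an estimate of what happened in this study. The core of the point does not depend on them. The power statement in the article is correct, and the choice of a single-arm pilot is not in itself an error. The fault is in treating a significant paired test as confirmation of a platform effect.

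**What to change.** Make these changes before the analysis begins. The article says that data collection has ended and analysis has not started.

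1. **Aims, Objectives, and Hypotheses.** Reword the hypothesis, main question and objective 2 so that the primary test estimates within-person change in QoL from baseline to t4 in caregivers given the platform-plus-wristband package. Naming t4 is safer than describing change during use, because a footnote to Table 1 places t4 one month after the intervention.
2. **Sample Size and Analysis.** State that confirmatory refers only to the ranking of the primary outcome for multiplicity, or replace it with primary estimate of change. Add that a significant result will not be reported as confirming a platform effect.
3. **Anticipated Findings.** Replace the sentence about the hypothesis being confirmed with a statement that the estimated change and its 95% CI will be used to plan a controlled study.

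No new analysis is required. A regression of QoL change on amount of platform use may look attractive but would not solve the problem: use is self-selected, and the article does not show that logs of use by content section exist.

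The cost is a few sentences. The downside is a less favourable headline claim.
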